## Abstract

**Background:**

To prevent age-related cognitive impairment, many intervention programs offer exercises targeting different central cognitive processes. However, the effects of different process-based training programs are rarely compared within equivalent experimental designs.

**Objective:**

Using a randomized double-blind controlled trial, this project aims to examine and compare the impact of 2 process-based interventions, inhibition and updating, on the cognition and brain of older adults.

**Methods:**

A total of 90 healthy older adults were randomly assigned to 1 of 3 training conditions: (1) inhibition (Stroop-like exercises), (2) updating (N-back-type exercises), and (3) control active (quiz game exercise). Training was provided in 12 half-hour sessions over 4 weeks. First, the performance gain observed will be measured on the trained tasks. We will then determine the extent of transfer of gain on (1) untrained tasks that rely on the same cognitive process, (2) complex working memory (WM) measurements hypothesized to involve 1 of the 2 trained processes, and (3) virtual reality tasks that were designed to mimic real-life situations that require WM. We will assess whether training increases cortical volume given that the volume of the cortex is determined by cortical area and thickness in regions known to be involved in WM or changes task-related brain activation patterns measured with functional magnetic resonance imaging. Dose effects will be examined by measuring outcomes at different time points during training. We will also determine whether individual characteristics moderate the effect of training on cognitive and cerebral outcomes. Finally, we will evaluate whether training reduces the age-related deficit on transfer and brain outcomes, by comparing study participants to a group of 30 younger adults.

**Results:**

The project was funded in January 2017; enrollment began in October 2017 and data collection was completed in April 2019. Data analysis has begun in June 2020 and the first results should be published by the end of 2020 or early 2021.

**Conclusions:**

The results of this study will help understand the relative efficacy of 2 attentional control interventions on the cognition and the brain of older adults, as well as the moderating role of individual characteristics on training efficiency and transfer.

**Trial Registration:**

ClinicalTrials.gov NCT03532113; https://clinicaltrials.gov/ct2/show/NCT03532113

**International Registered Report Identifier (IRRID):**

DERR1-10.2196/20430

## Introduction

### Background

Slowing age-related cognitive decline is a central concern for the prevention of pathological aging and loss of autonomy. Cognitive training has been identified as having significant potential in this context [1]. Many studies have identified working memory (WM) as a target for cognitive training because it is considered a foundational element of cognition. WM maintains and manipulates online information and supports many complex cognitive activities including language comprehension, reasoning, and mathematical abilities. Furthermore, aging and neurodegenerative diseases can impair WM, which has a negative impact on the ability to carry out high-level cognitive tasks. WM is a multicomponent system and relies on different attentional control processes (see [2] for a review), some of which have been the target of WM training programs. The goal of this study is to compare the effect of 2 attentional control training programs in older adults, each targeting major WM processes: inhibition and updating. A side-by-side comparison of inhibition and updating training programs will determine their respective and comparative impact.

We propose to measure the training program’s effect on proximal measures, as well as on transfer tasks and brain outcomes. Moving from proximal to transfer tasks is critical. A large number of studies have used updating training in older adults and found improvements on proximal tasks, (eg, [3-5]), with some generalization to switching tasks (eg, [6]). A few studies reported that inhibition training was effective when measured with inhibition tasks that were similar to those done in training [7,8]. However, little evidence was found to support generalization to untrained tasks. Thus, inhibition and updating training improve tasks that are similar to the training, but little is known about their effect on more complex tasks or comparative efficacy. It is important to determine whether improving one attentional process improves another, which would suggest within-WM generalization. In addition, tasks typically used to measure transfer rely on laboratory-based cognitive tasks, designed to reflect fine cognitive functions or processes. They are therefore not representative of the complexity present in everyday life. Thus, in addition to traditional complex WM tasks, transfer will be assessed using virtual reality, which can be used to reproduce real-life situations [9,10].

Neuroimaging can also provide critical information regarding brain processes engaged by the 2 training programs. Updating has been consistently associated with activation of the frontal and parietal lobes, including the dorsolateral and ventrolateral prefrontal cortices, the inferior parietal lobules, insula, and the premotor and supplementary motor areas [11-13]. Inhibition processes have been associated with the anterior cingulate cortex, middle frontal gyrus, inferior frontal regions, and parietal areas [14-16]. Functional neuroimaging studies have shown that updating training increases activation in the striatum, while reducing activation in areas of the frontal and parietal lobe, as well as in the anterior cingulate and temporal cortices, which would reflect better neural efficiency following training [17-19]. Less is known about inhibition training, but it has been found to be associated with increased cortical thickness [7] and decreased activation in the inferior frontal gyrus [7,20]. Given that updating and inhibition are both part of the same WM system, it is important that we compare the effects of different process-based training programs within a single experimental design. Neuroimaging will also be used to assess whether differences in brain structure or function at baseline explain interindividual differences in training efficacy as proposed in prior studies [18,21,22].

In addition, effects of cognitive interventions may vary because of individual factors influencing the rate and magnitude of training gain [23-27]. Pathophysiological factors, such as the volume of white matter lesions, are known to impair brain plasticity and reserve in older adults [28] and may modulate the efficacy of cognitive interventions. Efficacy may also be moderated by sex [29], intracranial volume [30], and genetics, as these factors affect resilience to cognitive aging. For example, a common single-nucleotide polymorphism (Val^66^Met) from the brain-derived neurotrophic factor (BDNF) tends to decrease BDNF and reduce neuroplasticity. However, very little is known about the influence of BDNF polymorphism on the efficacy of WM training for cognition and brain health. WM training could be more beneficial for the Met carriers because they show a reduced baseline performance for attentional control performance compared to the Val homozygotes. However, only the Val homozygotes show significant reduction in performance over a 10-year span [31], suggesting that they may also respond well to WM training. Catechol-O-methyltransferase (COMT) Val^158^Met is involved in dopamine degradation, which contributes to frontal modulation and cognition. For instance, carriers of the Val allele of the COMT polymorphism demonstrate reduced baseline performance [32,33], but may show larger performance gains from WM training than carriers of the Met allele [34]. Meanwhile, it was found that the brain activation decreases more in the prefrontal cortex of Met carriers after WM training [35]. Moreover, apolipoprotein ε4 (APOE-ε4) is known to increase the risk of Alzheimer disease.

### Objectives

The general goal of the study is to compare 2 process-based interventions, inhibition and updating WM training, and assess their effect on the cognition and brain of cognitively healthy older adults relative to an active control condition. There are 6 objectives to the study: (1) measure the gains on the trained tasks; (2) determine transfer of gain on (i) proximal measures that are not trained directly but reflect the trained process, (ii) complex WM measures, and (iii) virtual reality tasks designed to reflect WM in real life; (3) identify the effect of WM training on cortical thickness and task-related brain activation in regions known to be involved in updating or inhibition or both; (4) assess whether cognitive (eg, pretraining cognition), psychosocial (lifestyle, education, motivation), and biological markers (eg, white matter lesions, sex, genotype) moderate the effect of training on cognitive and brain outcomes; (5) examine dose effects by measuring training, transfer, and cerebral outcomes at different time points; and (6) assess if training reduces the age-related deficit on cognitive and cerebral measures.

### Hypotheses

It is hypothesized that older participants enrolled in WM training will show larger cognitive gains than those in the active control condition, and that gains will be specific to the cognitive process trained. We expect brain changes to be observed in regions that are associated with the trained process, with an overall decrease in activation due to improved neural efficiency for both functional magnetic resonance imaging (fMRI) tasks. It is expected that both trainings improve brain and performance parameters in older adults, which will increase to the levels of younger adults. Finally, it should be possible to identify individual factors that moderate the magnitude of the effect. The intervention may especially benefit participants with less advantageous cognitive and genetic profiles. However, these participants may require additional training for the intervention to be effective [26].

## Methods

### Trial Registration and Reporting Guidelines

The Attentional Control Training in Older People (ACTOP) study is registered with the US National Institutes of Health clinical trials registry (ClinicalTrials.gov identifier NCT03532113). The methodology of the protocol follows the Standard Protocol Items: Recommendations for Interventional Trials (SPIRIT) guidelines [36]. All the collected data are stored using an anonymized protocol.

### Study Design

The study design presented in Table 1 is a randomized double-blind controlled trial where older participants are randomly assigned to 1 of 3 parallel groups: inhibition, updating, and active control. In line with prior empirical work from our team showing transfer effects following attentional control training in older adults [37], training was provided in 12 30-minute training sessions over 4 weeks. All transfer measurements were completed once by a group of younger adults who did not receive the training. This is used to assess whether training helps increase performance and brain status of older adults to the level of younger adults. Given the large number of appointments, participants were recruited and trained in 5-6 waves. The study was carried out at the Research Center of the Institut universitaire de gériatrie de Montréal (CRIUGM).

**Table 1 table1:** Study design.

Schedule of events			Study period											
			Screening, baseline, and pretest		Intervention	Posttest 1	Intervention	Posttest 2		Intervention	Posttest 3	Intervention	Posttest 4	
Timepoint			V1	V2	V3–V5	V6	V6–V8	V9	V10	V11–V13	V14	V14–V16	V17	V18
**Enrollment**														
	Eligibility screen		X											
	Informed consent		X											
	Confirmation of eligibility			X										
	Randomization			X										
**Interventions**														
	Updating				X		X			X		X		
	Inhibition				X		X			X		X		
	General knowledge				X		X			X		X		
**Assessments**														
	**Clinical Assessments**													
		Montreal Cognitive Assessment (MoCA)	X											
		Logical Memory Test	X											
		Geriatric Depression Scale (GDS)	X											
		Ischemic Index	X											
		Cognitive Reserve Proxy Questionnaire (CRQ)	X											
**Training outcomes**														
	**Inverse efficiency score**													
		Updating			X		X			X		X		
		Inhibition			X		X			X		X		
**Proximal outcomes**														
	**Updating composite measure**													
		Keep track	X					X					X	
		Running span	X					X					X	
	**Inhibition composite measure**													
		Stroop Victoria	X					X					X	
		Anti-saccade	X					X					X	
**Complex working memory outcome**														
	**Working memory transfer**													
		Alpha span	X			X		X			X		X	
		Reading span	X			X		X			X		X	
	**Virtual car ride task composite measure**													
		Verbal memory	X			X		X			X		X	
		Visual detection	X			X		X			X		X	
**Brain structure**														
	Regional gray matter volume			X					X					X
	Cortical thickness			X					X					X
	Intracranial volume			X					X					X
	White matter lesions			X					X					X
**Brain activations**														
	Updating related			X					X					X
	Inhibition related			X					X					X
Salivary sample									X					

### Study Population and Eligibility Criteria

A total of 90 community-dwelling older adults (age 60-85) and 30 younger adults (age 20-35) were enrolled in the study. Older adults and younger adults were recruited in the Montreal area through advertisements in community centers, associations, local newspapers, and CRIUGM’s participants registry (*Banque de participants du*
*CRIUGM*). In addition, students, who were enrolled in an undergraduate laboratory course and wished to help with the study recruited younger adults among their acquaintances. Younger and older adults with similar educational levels were recruited in order to reduce the cohort effect on education.

Participants with the following criteria were included in the study: right-handed, fluent in French, and sufficient visual and auditory acuity to undergo neuropsychological testing. Participants were only included if they performed above the cut-offs on the delayed recall portion of the Logical Memory Test of the Wechsler Memory Scale for older adults. Performance on the Logical Memory Subtest was considered normal based on the following education-adjusted cut-off scores used in the Alzheimer’s Disease Neuroimaging Initiative (ADNI) study: 9 or more for 16+ years of education; 5 or more for 8-15 years of education; 3 or more for 0-7 years of education [38-40].

Participants were excluded from the study if they had received a diagnosis of a disease or injury of the central nervous system (ie, moderate to severe chronic static leukoencephalopathy [including previous traumatic injury], multiple sclerosis, neurodevelopmental disorders, subdural hematoma [past or current], subarachnoid hemorrhage, primary cerebral tumor or cerebral metastases, epilepsy, dementia or other neurodegenerative diseases, stroke, intracranial surgery or major surgery within the last 2 months), alcoholism or substance abuse, general anesthesia in the past 6 months, serious comorbid conditions, major depression or anxiety, schizophrenia, or other major psychiatric disorders (eg, bipolar disorder). Participants were also excluded if they were unable to undergo an MRI scan, due to medical contraindications, or tolerate the procedure. Older adult participants were excluded if they reported subjective cognitive decline [41], such as feeling their memory is worse than it used to be and that it worries them, or if they had previously participated in structured attentional control training. Despite the time required for the participants to carry out the study, no change in the habits of daily living was required, except to abstain from cognitive training during the intervention. The younger adults were only included in the study if they were no longer full-time students. This constraint was intended to increase the diversity of age and education in our sample of younger participants in order to better match the diversity of our sample of older subjects. Moreover, it was not possible to determine the final level of education of the students, many of whom were actively involved in training programs that have made them experts in metacognitive strategies.

### Procedure

After a first telephone contact to assess global eligibility, potential participants were invited to the laboratory to consent to participate in the study, complete standardized clinical and neuropsychological assessments, and the outcome measurements for the baseline (V1; see list in Table 1). A brain imaging examination for the baseline was completed the following week (V2). Eligible participants were given CAD 50 (~US $38) at each brain imaging session, for a total of CAD 150 (~US $114) for older adults and CAD 50 (~US $38) for younger adults.

Data on proximal cognitive and brain outcomes were collected at 3 timepoints: no more than 2 weeks prior to training for the baseline (PRE), between training sessions 6 and 7 (POST2), and no more than 1 week following the end of training (POST4) for the postbaseline tests. Complex WM outcomes were measured at 5 time points: (1) at PRE; (2) after the third training session (POST1), (3) at POST2, (4) after the ninth training session (POST3), and at (5) POST4. The complex WM outcomes at POST1 and POST3 were completed on the same day as a training session to reduce travel and the number of visits to the laboratory. The standard duration of the study was 8 weeks and involved 18 appointments. Participants were informed that the study must be performed without discontinuity. A postponement of up to 1 week was exceptionally authorized in the event of unforeseen circumstances. To limit the influence of the circadian rhythm on performance, training sessions and assessments were performed at similar times of day (ie, morning or afternoon) for a given participant. In addition, at the end of the first appointment, a personalized calendar containing all dates and durations of appointments was given to each participant in paper format. A reminder email (or a phone call made if no email address was available) was also sent the day before each MRI appointment.

### Randomization and Blinding

Participants meeting eligibility criteria were randomly assigned to 1 of the 3 interventions. An independent project coordinator, who was not involved with the enrollment process, cognitive assessments, or interventions, generated blind randomized samples without replacement. Randomization allocated eligible participants individually to 1 of the 3 training conditions using a computer-based random digits program (ie, one participant at a time as they enter the study). In this double-blind study design, participants were blind and unaware of the experimental and control conditions, as they were instructed that different capacities were trained in different programs. Assessors were blind to the participants’ intervention condition. If a participant accidentally shared information that may identify their intervention group to an assessor, the incident was recorded and a different assessor was assigned for this participant for the following assessments. Training supervisors were aware of the intervention assigned to the participants. All participants were assigned 2 anonymized identification numbers: one known by the training supervisors only and the other known by the assessors only. For simplicity, the counterbalancing for the tasks’ versions of transfer outcomes was done upstream for each age group separately, using a replicated Latin square design, regardless of the older adults’ intervention.

### Interventions

The 2 experimental training conditions (inhibition and updating) were provided by the Neuropeak web platform ([name] et al, unpublished data) using a Samsung Galaxy Tab 2 (Android version 4.2.2).

The updating training involved 2 N-back-type exercises (1-2- and 3-back) with different sets of stimuli. Both sets were performed during each of the 12 training sessions. The first set comprised stimuli made from digits (1 to 9) and the second comprised symbols (moon, planet, star, dog, bird, snake). The stimuli were displayed on the center of the screen, one by one, at the rate of 4 seconds per item (Figure 1A). In both sets, participants were asked to indicate whether each item matches the one presented in the *n* position previously (eg, 3-6-3-9-9 wherein the second “3” is the only match in a 2-back block). Each round comprised 8 blocks grouped by N-back level and performed in the following order: 1-back (2 × 11 trials), 2-back (3 × 12 trials), and 3-back (3 × 13 trials). Each of the 8 blocks were set to include 40% “match” responses. Nonetheless, participants were able to reach the 3-back level only if their accuracy was equal or above 75% at the 2-back level. If they were below this percentage, they finished the round with a 1-back block instead. Participants were instructed to respond as fast as possible. “Match” and “Mismatch” buttons were permanently displayed on the right side of the screen and participants were required to answer with their right thumb.

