**Figure 1 figure1:**
[figure not shown]
Illustration of the training exercises used to train attentional control: (A) in this Neuropeak updating exercise, the task consisted of indicating whether the current symbol (eg, a star) matches (or does not match) the previously displayed symbol in 1-, 2-, or 3-back position. (B) In this Neuropeak inhibition exercise (incongruent trials), the task consisted of indicating the number of copies (eg, 5) of the digit displayed in the center of the screen (eg, 2). (C) In this general knowledge quiz game, the task consisted of indicating the number of the correct answer (eg, 4) to the question displayed in the upper part of the screen.

Inhibition training also involved 2 Stroop-like exercises with different sets of compound stimuli. Both sets were performed during each of the 12 training sessions. The first set comprised compound stimuli made from digits (1 to 6) and the second included compound stimuli made from letters (D, F, H, L, S, T). The 2 different sets were used to reduce the stimulus–response dependency of the improvement in performance on tasks, and hence facilitate transfer. Stimuli was displayed in the center of the screen (Figure 1B). In the first set, participants were asked to count the number of items in each trial while in the second set, they were asked to identify the largest letter. In each set, they were presented 3 types of stimuli: congruent (eg, 5 copies of the digit “5” or a large “H” formed from smaller Hs), neutral (eg, five copies of the symbol “*” or a large “H” formed from smaller “*”), and incongruent (eg, 5 copies of the digit “3” or a large “L” formed from smaller Hs). Each of the 2 sets comprised 7 blocks. The first block contained 20 congruent compound stimuli, the second block contained 60 neutral stimuli, and the third 60 incongruent compound stimuli. Incongruent items require inhibiting the smaller stimuli to determine the larger one. The congruent and incongruent blocks were then repeated twice in alternance. Participants were instructed to respond as fast as possible while maintaining high accuracy. Response keys were displayed on both sides of the touchscreen, and participants responded with their thumbs. Participants were instructed that there was no time limit but responses taking longer than 4 seconds were not recorded to avoid the impact of outliers. A response immediately triggered the following target in order to reduce the contribution of task preparation to performance.

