### Effect on the Trained Tasks

The improvements on the trained tasks will be reported using inverse efficiency scores (IESs) for each participant, which corresponds to the mean of the reaction time per session divided by the proportion of error minus one. These scores will be calculated for the 1-, 2-, and 3-back blocks separately for the updating training and separately for congruent and incongruent blocks for the inhibition training.

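### Gain on the trained updating task rests on the inverse efficiency score alone, which can register a speed-accuracy shift as improvement

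*Protocol article*

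**What the plan says.** All references are to the protocol article.

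- *Effect on the Trained Tasks*: "The improvements on the trained tasks will be reported using inverse efficiency scores (IESs) for each participant", a score "which corresponds to the mean of the reaction time per session divided by the proportion of error minus one". For the updating arm, "These scores will be calculated for the 1-, 2-, and 3-back blocks separately for the updating training".
- *Analysis of Behavioral and Brain Outcomes*: this score is the dependent variable for training improvement. The updating model is session (12 levels) by N-back level (3 levels), fitted to that arm on its own. No accuracy, hit, false-alarm or sensitivity measure is named for the trained tasks.
- *Interventions*, updating exercise: the blocks are "1-back (2 × 11 trials), 2-back (3 × 12 trials), and 3-back (3 × 13 trials"), and "Each of the 8 blocks were set to include 40" per cent matches. The instruction is "Participants were instructed to respond as fast as possible". The one accuracy rule is that "participants were able to reach the 3-back level only if their accuracy was equal or above 75% at the 2-back level".
- *Interventions*, inhibition exercise: the instruction is fuller: "Participants were instructed to respond as fast as possible while maintaining high accuracy".
- *Interventions* also describes correct/incorrect colour feedback after each response and an end-of-session graph of the trainee's progress. The Figure 2 legend identifies the plotted score as the inverse efficiency score.
- *Transfer to Proximal Outcomes*: the primary updating composite combines keep track and running span, both untrained tasks scored as proportion correct.

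**The concern.** A ratio of speed to accuracy cannot show which of the two moved. Over 12 sessions a trainee may update better. The trainee may also respond faster at the cost of more errors, or drift towards the more frequent response. All three can lower the score.

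Three features of the updating exercise make this more than a formality. Mismatch is correct on 60% of trials, so a bias towards it costs little accuracy. The instruction as printed mentions speed and not accuracy. The test is made within one arm, so no comparator separates better updating from general speeding or a change of response criterion.

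What is at stake is Objective 1 for the updating arm and how transfer is read against it. If transfer is absent, the reader needs to know whether the trained process improved and did not generalise, or never improved. The score alone cannot settle that.

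**Working it through.** **Inputs from the article.** Match share 40%; block lengths 11, 12 and 13 trials at 1-, 2- and 3-back; a 75% accuracy rule at 2-back for entry to 3-back; the score. As printed, the formula in *Effect on the Trained Tasks* gives RT/(error proportion − 1), which is negative. I read it as RT/(1 − error proportion), that is RT/accuracy, in line with the description of the progress graph in *Interventions*.

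**Inputs assumed.** RT and accuracy levels, because the article gives none. Starting accuracy is taken as 80% to 100%; the RTs are illustrative.

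**1. The 40% figure.** If the first n items of a block cannot match, each block has 10 scorable trials (11 − 1, 12 − 2, 13 − 3). Four matches in 10 give 40% at every level, which reproduces the stated share.

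**2. Constant Mismatch pressing.** Accuracy = 1 − 0.40 = 60%, with a hit rate of 0 and balanced accuracy of 50%. If the first n items also count as mismatches, accuracy is 7/11 = 63.6%, 8/12 = 66.7% and 9/13 = 69.2%.

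**3. Break-even.** The score improves if RT1/RT0 < accuracy1/accuracy0. The RT fall needed when accuracy drops to 60% is 1 − 0.60/accuracy0:

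| Starting accuracy | RT must fall by more than |
|---|---|
| 80% | 25.0% |
| 85% | 29.4% |
| 90% | 33.3% |
| 95% | 36.8% |
| 100% | 40.0% |

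From 1000 ms at 90% (score 1111), constant pressing scores 400/0.60 = 667 at 400 ms (40% better), 600/0.60 = 1000 at 600 ms (10% better) and 700/0.60 = 1167 at 700 ms (5% worse).

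**4. A milder trade-off.** 1400/0.92 = 1522 and 1000/0.80 = 1250, an improvement of 1 − 1250/1522 = 18%. With equal error rates on matches and mismatches, d' = z(hits) − z(false alarms) falls from 2.81 (0.92 against 0.08) to 1.68 (0.80 against 0.20). The break-even RT for this accuracy loss is 1400 × 0.80/0.92 = 1217 ms, so a slower response than that at 80% would worsen the score. Similarly, going from 1000 ms at 90% to 80% accuracy gives 850/0.80 = 1062 (better than 1111) but 900/0.80 = 1125 (worse).

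**5. The 75% rule.** Constant pressing at 2-back (60%, or 66.7% on the wider count) falls below 75%, so that trainee produces no 3-back score. The 80% responder passes. The rule tests 2-back accuracy only; no floor is stated for 1-back or within the 3-back blocks.

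**The case against.** The score divides by accuracy, so errors are penalised, and large accuracy losses need large RT falls to pay. Trial-by-trial feedback, praise for runs of correct answers and trainer supervision all discourage careless pressing. The 75% rule keeps constant pressing at 2-back out of 3-back. The objective concerns gain on the trained tasks, and whether updating improves is tested separately on an accuracy-based composite against an active control. Nothing makes the transfer analyses conditional on the training score. Component RT and accuracy might also be reported in an analysis plan that is not shown.

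Most of this stands, and it rules out several stronger readings that a reader might infer:

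- That the score cannot measure updating in this task, or that faster and less accurate responding always counts as gain. It does so only past the break-even.
- That accuracy cannot fall below 60%. That value belongs to constant Mismatch pressing; random pressing averages 50% and constant Match pressing 40%.
- That the primary result is compromised. The updating composite does not use this score.
- That trainees actually responded this way. Nothing in the article shows it.

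The objection does not remove the point. The article does not leave the trained-task outcome open: it names one dependent variable. Feedback is offset in part by a progress graph that plots the same score, so a trade-off past the break-even is shown to the trainee as progress. The 92% to 80% shift passes the 75% rule and can occur at every level.

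**Conclusion.** The concern holds in limited form. For the updating arm, the only stated measure of Objective 1 can improve when RT falls proportionally more than accuracy, with discrimination of matches unchanged or worse, and the within-arm model has nothing to reveal it. Constant Mismatch pressing needs an RT fall of more than 25% to 40% from starting accuracies of 80% to 100%, and matters mainly at 1- and 2-back. Milder shifts need less: more than 1 − 0.80/0.92 = 13% for 92% to 80%.

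These sizes rest on assumed RT and accuracy levels, on 10 scorable trials per block and, for d', on equal error rates on matches and mismatches. That last example shows a general speed-accuracy trade-off; only constant pressing draws on the 40/60 split. The effect is confined to a non-primary objective and to how transfer findings are interpreted beside it. Adding measures is justified; replacing the score outright would be a matter of preference.

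**What to change.** In *Effect on the Trained Tasks* and the matching paragraph of *Analysis of Behavioral and Brain Outcomes*, keep the inverse efficiency score and analyse beside it, for each N-back level:

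- d' from hits and false alarms, pooled over blocks and stimulus sets within a session, with a standard correction for rates of 0 or 1;
- RT of correct responses.

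If hits and false alarms were not logged separately, which the article does not settle, use proportion correct in place of d'.

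State the reading rule in advance: a lower score is interpreted as improved updating only if d' (or accuracy) rises, or if RT falls with d' (or accuracy) not lower. Otherwise it is described as a speed-accuracy shift.

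The cost is two further measures per level and no new data collection, provided trial-level responses with trial type were kept. d' will be imprecise at 1-back, where a round has only 2 × 4 = 8 matches.
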